### 3. Methods: Assignment of interventions

#### 3.1. Allocation (sequence generation, concealment, and implementation)

Participants will be randomly assigned to the intervention or control group with a 1:1 allocation as per a computer-generated randomization sequence created by study statistician, co-I [name], and stratified by center, age (2-7, 8-12,  $\geq 13$  years old), and type of cancer (hematological, non-hematological malignancies). Study personnel will not have access to the sequences. Random sequences will be embedded in REDCap by informatics personnel, ensuring best practice standards for allocation concealment. Two weeks after enrolling, at week 0, if participant meets the criteria of being a responder, i.e. having answered two or more PQ-surveys, regardless of who in the dyad answered them, the RC will be able to see study arm assignment in REDCap. The RC will begin intervention procedures by turning on the PQ-feedback report and email features of PQ web,

notifying the primary team and linking the account to the corresponding providers (primary oncologist, primary nurse, primary psychosocial clinician, and PC Response team key person) so they start to receive reports too, and letting the PC Response team administrative designated person know of the assignment so they can schedule the initial visit with the Response team (as explained in 2.3.1 and Figure 7).

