## 1.3. Trial Design

We will conduct a randomized, controlled, un-blinded, multisite, effectiveness trial with two parallel groups, PQ Response (intervention) vs. usual cancer care (comparator or control). Primary outcomes will be the mean over 16-weeks of the child HRQoL total score reported by (a) the parent and (b) the patient if ≥5 years of age. Randomization will be stratified by site, age, and type of cancer with a 1:1 allocation. We intend to enroll a total of 200 expecting to achieve our target sample size of 136 pediatric oncology patients ≥2 years old with advanced cancer (N=68/arm) from five participating sites over a 36-month period (start times staggered by site, see more in section 2.6 Sample size). The expected start for enrollment is September 2017.

Families (patient and one of the parents) will be enrolled for a total of 18 weeks. After an initial 2-week run-in period, families who answered a total of at least two PediQUEST surveys per participant during the run-in period (responders), will be randomized to the intervention or usual care (Figure 4).

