The 2-week run-in period is established to identify and exclude non-responder dyads before randomization to decrease the frequency of missing data for the primary outcome. Non-responders are defined as those who of the three PQ-Surveys assigned during the run-in period have <2 answered. PediQUEST-Surveys will be considered answered if the survey could be scored, i.e. a survey with >50% of the questions answered. Both patient and parent must be responders for the dyad to continue. Pilot data showed that participants who did not register in the PediQUEST web system did not differ from those in the responder group in terms of diagnosis, age, or survival. The 16-week follow-up period was defined for practical reasons. From our prior work we know that (a) short enrollment periods, enhance recruitment and retention; and (b) intermittent attrition increases

[figure not shown]

over time, especially after 20 weeks. Considering the intra-subject variability of HRQoL scores over time, we chose a 16-week period to allow for a more precise measure of the main outcome while aiming to improve enrollment and intermittent attrition. In addition, pilot data showed the need to allow enough time for intervention effects to be demonstrated (for example a preventive measure only takes effect when the next treatment cycle begins) making shorter follow-up less advisable. Finally, the 16-week period also poses an acceptable burden on PC teams whose workload will be increased without a corresponding increase in staff.

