## 2.5. Participant timeline

Participants' timeline is presented in Figure 8. Study participants will be assessed using the PediQUEST web system. At all sites, immediately following consent, the RC will help families register in the system and download the mobile App. All participating parents will be provided with a PQ account, linked to an email of choice. In the case of children aged 2 to 4 years old, only parents will answer PediQUEST Surveys. In the case of children aged 5 to 7 years old, parents and children answer PediQUEST Surveys which are sent to the parent's account; it is expected that parents read the questions out loud to the child. Patients  $\geq 8$  years old will be provided with a PQ account of their own (will need a different email than the one provided by their parent) and will answer PQ-Surveys on their own; in addition, their parents will answer proxy versions (see section 2.5.1). Once a PQ-Survey is assigned, a link is sent by email/notification to the corresponding PQ account owner. In addition, questionnaires can be handed over to participants using the research team tablet for completion, or answered over the phone (administered by the RC) if the participant prefers. PQ Reports will only be available for participants assigned to the intervention arm during the 16 weeks after randomization. After registration, the RC will manually assign the Baseline Packet (30 minutes, online parental survey, preferably answered at the clinic or ward at the time of enrollment). Over a total of 18 weeks (2-week run-in period and 16-weeks post-randomization follow-up), parents and patients  $\geq 5$  years old in both arms will be automatically assigned weekly PediQUEST surveys (10 minutes each, online self-administered surveys answered from any location, provided there is access to internet connection). In addition, parents of both arms will be assigned Monthly Parent Questionnaires evaluating distress, burden, and use of complementary therapies every 4 weeks (15 minutes, online surveys answered independently), beginning at the time of randomization as indicated in Figure 8. Parent Activation Surveys will also be administered at weeks 8 and 16 (the measure at week 8 will be used for an exploratory mediation analysis described in the analysis section 4.3.2.5). Medical records will be abstracted by RCs every four weeks. All patients  $\geq 8$  years old and parents who completed the 16-w follow-up, dropped out, and parents of children who died, and a convenient sample of providers, will be invited to participate in an Exit Interview (in-depth face-to-face or phone interview) administered by the RCs to evaluate study processes, care experience, and intervention fidelity (among those in the intervention arm). There are two points in the timeline with potential for delays. Technical issues, such as troubleshooting access to PediQUEST with participants, or other technical mishaps (which we expect to be rare events), may prolong the run-in period by one or two weeks. In addition, the scheduling of exit interviews will always occur out of the 16-week follow-up period, most frequently within the next week after the last survey is answered, but adapting to the family availability. When a patient dies within the study, the invitation for the exit interview, as explained below, is sent 12-weeks after the death. For these reasons, total enrollment time will be 18 weeks in most cases, but there will be exceptions. This will be explained during the enrollment process.

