**Table 3. Study Instruments**

| Baseline Packet (week -2, right after consent)                      |                             |                                                                                                                                           |                                                                                                                                                                                                                                                                                                                                                                                                                                                                                                                                                                                                                                                    |
|---------------------------------------------------------------------|-----------------------------|-------------------------------------------------------------------------------------------------------------------------------------------|----------------------------------------------------------------------------------------------------------------------------------------------------------------------------------------------------------------------------------------------------------------------------------------------------------------------------------------------------------------------------------------------------------------------------------------------------------------------------------------------------------------------------------------------------------------------------------------------------------------------------------------------------|

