## 4.3. Statistical methods

### 4.3.1. Overview

All statistical analysis will be conducted on an intention-to-treat basis, i.e. all randomized participants with baseline and at least one post-baseline measurement will be analyzed by original treatment assignment, regardless of adherence. Baseline characteristics will be described and compared between groups using summary measures (e.g. means, medians, rates) and tests selected based on variable distribution. Analyses will be adjusted for factors used in the stratified randomization (center, age group and type of cancer). In addition, if, despite efforts to standardize intervention delivery (section 5.1), we identify substantial differences in fidelity across sites, we will evaluate effect modification by site including the site  $\times$  intervention interaction in the models. The False Discovery Rate criterion will be used to correct for multiple testing in non-planned analyses. Co-I [name] has been the primary biostatistician for all prior PQ analyses and is best suited to head the PQ Response's analysis, along with her team at Deakin University. The PI and Co-I [name] will be part of the leadership team. While all Co-Is will be involved in analysis and manuscript writing, some may take a more prominent role according to their specific expertise (e.g. [name], [name] with aim 2, and [name] with aim 3). DFCI will coordinate data cleaning and programming.

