### 4.3.2. Analysis Plan

#### 4.3.2.1. Comparison of patient-level outcomes (HRQoL and Symptom distress) - Specific Aim 1

The effect of the intervention on child quality of life and symptom burden outcomes (see section 2.4) will be estimated using mixed linear models, with patient as a random effect and group, time (categorical) and group x time interaction and the stratification factors as fixed effects. . The same analysis will be undertaken for the respective domain subscales of PedsQL (physical and psychosocial) and PQ-MSAS (physical and psychological).

#### 4.3.2.2. Comparison of parent-level outcomes (anxiety, depression, HRQoL, and burden) - Specific Aim 2

The same analytical approach described for patient-level outcomes will be followed to analyze parent S-TAI-State, CES-D-10 mean scores and aRSQ symptom-related scores. In S-TAI-State analysis, we will additionally adjust by baseline S-TAI-Trait score. We will also compare depression (CES-D-10  $\geq 10$ ) over time between the two groups using generalized linear mixed models with logit link and binomial distribution. As gender is a predictor of these outcomes, it will be included in these models if imbalanced between arms.

#### 4.3.2.3. Comparison of family activation outcomes - Specific Aim 3

Mixed models, similar to those described for patient-level outcomes, will be fitted to estimate the effect of the intervention on change between week 16 and baseline in Brief COPE active coping, planning, and instrumental support Scores, Total No. of, and No. of different, complementary therapies, and No. of psychosocial clinician encounters over the 16-w study period. Link and distribution for these models will be defined based on the distribution of the outcome variable. We will explore whether change in parent's activation score is modified by parent/child characteristics (e.g. parent's gender, S-TAI-Trait, CES-D-10 scores; and child's diagnosis, among others) including the corresponding interaction terms.

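### The arm is released on answered PQ-Surveys alone, so the only pre-treatment Brief-COPE and aRSQ-Stress values can be given after the family knows its allocation, or be missing

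*Protocol*

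**What the plan says.** **Release condition.** Section 3.1 makes the arm visible two weeks after enrollment "if participant meets the criteria of being a responder, i.e. having answered two or more PQ-surveys"; it does not matter which member of the dyad gave the answers. Section 1.3 says that "families who answered a total of at least two PediQUEST surveys per participant during the run-in period (responders), will be randomized". Section 1.3.1 gives the complement: "Non-responders are defined as those who of the three PQ-Surveys assigned during the run-in period have <2 answered". Section 2.3.1 lets the Principal Investigator and Project Manager waive the responder criterion in rare cases. All of these refer to PediQUEST Surveys, and none names the Baseline Packet.

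**Timing of the packet.** Table 3 schedules it as "Baseline Packet (week -2, right after consent". Section 2.5 has the research coordinator assign it by hand and describes it as "preferably answered at the clinic or ward at the time of enrollment". Section 2.7 allows remote consent.

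**Use of the packet.** Brief-COPE change from baseline is an Aim 3 outcome, and symptom-related stress (aRSQ-Stress) at study entry and week 16 is an Aim 2 outcome (section 2.4.2.2). Section 4.3.2.2 adds: "In S-TAI-State analysis, we will additionally adjust by baseline S-TAI-Trait score". Section 4.3.1 defines the analysis set as "all randomized participants with baseline and at least one post-baseline measurement".

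**Blinding.** Section 3.2 states that participants and staff know the allocation once randomization has taken place.

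**The concern.** A change score needs a baseline that treatment cannot have touched. The intervention sets out to activate parents, and Brief-COPE is the measure of that activation. Section 2.3.1.1 recommends the first Response team consultation within 3 weeks of randomization and includes parent activation activities in it.

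If a parent still has an open packet at week 0, the rule in section 3.1 does not hold the allocation back. The parent can then answer coping and stress questions knowing the arm, and possibly after that first visit. Such a value may already contain part of the effect in the intervention arm, or a reaction to the allocation in either arm. No later analysis can restore an untouched baseline. If the packet is never submitted, these two outcomes have no baseline for that dyad.

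**Working it through.** No stated figure decides this point. It rests on setting the rules side by side, with a small calculation to bound the size.

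**1. Does anything else tie the packet to release?** Section 2.7 requires the coordinator to assign the packet at registration, not to confirm its completion before week 0. The automatic submission after 48 hours in section 2.3.1.1 is described for the weekly PQ-Surveys and is not extended to the packet. No closing date and no rule specific to a late packet are stated.

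**2. Which outcomes depend on the packet?**

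| Measure | Other pre-treatment value | Depends on packet? |
|---|---|---|
| Brief-COPE | None (otherwise weeks 8 and 16) | Yes |
| aRSQ-Stress | None (otherwise weeks 8 and 16) | Yes |
| S-TAI-Trait (covariate) | None, but Table 3 describes it as stable over time | Little if late |
| S-TAI-State, CES-D-10 | Scheduled at week 0 in the monthly questionnaires | Not for the outcome value |
| Complementary therapies, psychosocial encounters | Parent report every four weeks; chart counts | No |
| PedsQL (primary) | Run-in surveys | No |

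**3. Power if packets are missing.** Inputs from section 2.6.1: n = 68 per arm, Brief-COPE effect d = 0.5 (0.75 points, SD 1.5), one-sided alpha 0.05, stated power 80%. With the normal approximation, power = Φ(d·√(n/2) − 1.645).

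- n = 68: 0.5 × √34 = 2.916; 2.916 − 1.645 = 1.271; power 89.8%. The stated 80% is not reproduced, but it errs on the low side and does not bear on this point.
- 5% missing (assumed): n = 64.6, power 88.4%.
- 10% missing (assumed): n = 61.2, power 86.9%.
- 20% missing (assumed): n = 54.4, power 83.2%.

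The exact t-test gives 89.5% at 68, 86.5% at 61 and 82.8% at 54 per arm.

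**4. Dilution if packets are late.** Let p be the share of packets completed late and f the share of the 16-week effect already present in a late intervention-arm baseline. The difference in change is then estimated as 0.75 × (1 − p·f). Both p and f are assumptions.

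- Worst case, f = 1: 0.75 × 0.95 = 0.71 at p = 5%; 0.75 × 0.90 = 0.675 at p = 10%; 0.75 × 0.80 = 0.60 at p = 20%.
- Milder case, f = 0.25 and p = 10%: 0.75 × 0.975 = 0.73.

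**The case against.** The strongest reply is that the timing is already fixed. Table 3 puts the packet right after consent, two weeks before the arm is visible, so completion after week 0 would be off schedule. In section 2.5 the preference attaches to answering in clinic at enrollment; it does not license completion after randomization. Completeness is also watched: the packet sits in PQ web (section 4.1), PQ web data are reviewed daily for completeness (section 5.3), and weekly and monthly data-quality reports follow (sections 4.2 and 5.1.2). All of this stands and makes late packets less likely. It does not make submission a condition of seeing the arm.

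A reader might infer that a dyad without a packet drops out of all Aim 2 and Aim 3 analyses. The protocol does not support that. Most of those outcomes have their own data, section 4.3.1 does not equate baseline with the packet, and section 4.3.3 offers multiple imputation or inverse probability weighting. A missing S-TAI-Trait leaves only a covariate gap.

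A reader might also infer a serious loss of power or a 10% dilution. Neither is shown. The late or missing share has no source in the protocol. Power at an assumed 20% missing still exceeds the stated 80%. Full dilution requires a late baseline to carry the whole 16-week effect, although section 1.3.1 says that effects need time to appear.

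Finally, a strict condition could delay or lose randomizations, and with them primary-outcome data, for the sake of secondary baselines. The run-in extension of one or two weeks in section 2.5 is for technical problems, and a pause under section 2.3.1 needs Principal Investigator approval. This is a fair objection, and the fix must provide for it.

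**Conclusion.** The point holds for two secondary outcomes, Brief-COPE change and aRSQ-Stress. The protocol schedules their only pre-treatment measurement before randomization but does not require it before the arm is shown. What releases the allocation is a conduct rule set in section 3.1, so it cannot be left to the analysis.

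The wording of section 3.1 adds to the exposure. By counting surveys whichever member of the dyad answered, it would release the arm with no parent response at all, whereas section 1.3.1 requires both patient and parent to be responders. The two should be reconciled.

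The size is unknown. Under assumed shares of 5% to 20%, the power loss is modest (89.8% to between 88.4% and 83.2%), and the worst-case estimate of a 0.75-point effect lies between 0.71 and 0.60. The case for change rests on an avoidable risk of bias and a cheap remedy, not on demonstrated harm. It is worth fixing but does not threaten the primary result.

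**What to change.** 1. In section 3.1, add to the REDCap release condition, beside the responder check, that the Baseline Packet has been submitted, or at least its Brief-COPE and aRSQ-Stress parts.
2. Allow a documented waiver by the Principal Investigator and Project Manager, on the model of the one in section 2.3.1, so that a responder dyad that never submits is not lost from the primary outcome.
3. Record the packet's submission time. State that a packet stamped after release is not used as a baseline for Brief-COPE or aRSQ-Stress and is handled as missing under section 4.3.3.

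The cost is one branching condition and two or three sentences. The downside is that a few dyads wait some days for randomization. Dyads recruited before the change can still be classified if PQ web kept the submission time.

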### 3.2. Blinding

After randomization, participants, PC team, oncologists, and research staff will be unblinded to group assignment, because the intervention is not amenable for blinding.

## 4. Methods: Data collection, management, and analysis

### 4.1. Data collection methods

Research material for this study primarily involve patient reported outcomes and parent reports collected and stored electronically through the PQ web system. In addition, RCs will collect data for tracking purposes (with electronic (REDCap) and/or paper and pencil checklists and personal notes), do the medical record abstraction (online), and conduct the semi-structured exit interviews. Data collection protocols are identical for both arms and were described in section 2.5, participant timeline, together with instrument's psychometric properties. A sample of study instruments is presented in the Appendix.

REDCap is a web-based application that allows for the creation and management of online databases. We will run the study's enrollment tracking system and randomization module on this platform. PQ web is a web-based application that allows for the use of PROMs, includes scheduling, reminder, and scoring and feedback capabilities. The PQ Response's Baseline Packet, PQ-Surveys, Monthly Parent Surveys, and the Medical Record Abstraction will be collected through this system. Participants can use the PQ mobile application to answer surveys and view reports; providers can also download the App and use it to view patient reports. Both systems can handle multicenter studies and easy transfer to common statistical packages. The semi-structured exit interviews will be conducted face-to-face or over the phone and audio-recorded.

All participating sites will designate an RC who will be trained in all study procedures (9 hours including role play), participate in monthly meetings, generate reports of research activities, prepare and maintain IRB documentation, enroll participants, and be in charge of the communication with oncologists and Response teams regarding subjects' participation. Strategies to enhance retention have been described in section 2.3.2, adherence.

### 4.2. Data management

The Dana-Farber Cancer Institute in Boston will serve as the Study Data Center (SDC), and will be responsible together with the study Data and Safety Monitoring Board (DSMB) for providing a specific data collection and monitoring system, including the design of the Data Management Plan, Standard Operating Procedures (SOPs), Data Validation Plan, study data collection and completion guidelines for investigators, supervising data collection procedures, assuring maintenance of high quality databases, and arranging an efficient and safe

transfer of non-electronic study data, in compliance with Good Clinical Practices (GCPs). RCs and local PIs will be responsible for the local data centers (LDC) at each site and will communicate with the SDC on a routine basis. RCs will be trained in data management procedures and GCPs before starting enrollment.

Each eligible participant (child and parent) will be assigned a unique study identification number. REDCap will be used to collect data during participants' recruitment (see 2.7). Most study data will be collected and stored electronically through REDCap and the PQ web system. All other source documents, exit interviews' audio files and transcripts, *pool list* and other tracking forms, with the exception of consent documents, will be created as or converted to electronic format (e.g. audio files will be mpg4, transcripts of interviews .doc, palliative care clinical notes will be saved as pdf files). Data managers and study statisticians will always use de-identified datasets when generating study reports or conducting interim and final analysis. Details about data storage and how we plan to preserve subjects' confidentiality together with security features are explained in section 6.3.

A comprehensive tracking system will be implemented at the local and study data centers. Data quality reports will be generated on a weekly basis. Whenever an inconsistency is detected, it will be solved by the site RC and entered into the database by the PM at the SDC. The PM will audit inclusion, recruitment, and medical record abstraction processes by comparing inclusion / eligibility forms, and data abstracted from charts against medical records on a random sample of 10% of all screened subjects.

At the end of the study, and after a comprehensive quality check and assurance, the final data validation will be run. If there are no inconsistencies, a pre-lock checklist will be used and completion of all data management activities will be confirmed. Once the approval for locking is obtained from all key project stakeholders, including the study statistician, the database will be locked and clean data will be extracted for statistical analysis. The database will not be changed in any manner after locking.

